**Methods/Design:**

This randomised, double-blind, placebo-controlled trial will involve 200 participants with CRCP recruited from medical practices, outpatient departments and the community via print and radio media. Participants will be randomly allocated to a physiotherapy or placebo group using concealed allocation stratified by treating physiotherapist. Both groups will receive 10 sessions of individual standardised treatment over 10 weeks from one of 10 project physiotherapists. For the following 12 weeks, the physiotherapy group will continue a home exercise program and the placebo group will receive no treatment. The physiotherapy program will comprise shoulder joint and spinal mobilisation, soft tissue massage, postural taping, and home exercises for scapular control, posture and rotator cuff strengthening. The placebo group will receive inactive ultrasound and gentle application of an inert gel over the shoulder region. Blinded assessment will be conducted at baseline and at 10 weeks and 22 weeks after randomisation. The primary outcome measures are self reported questionnaires including the shoulder pain and disability index (SPADI), average pain on an 11-point numeric rating scale and participant perceived global rating of change. Secondary measures include Medical Outcomes Study 36-item short form (SF-36), Assessment of Quality of Life index, numeric rating scales for shoulder pain and stiffness, participant perceived rating of change for pain, strength and stiffness, and manual muscle testing for shoulder strength using a handheld dynamometer. To evaluate cost-effectiveness, participants will record the use of all health-related treatments in a log-book returned to the assessor monthly. To test the effect of the intervention using an intention-to-treat analysis, linear regression modelling will be applied adjusting for baseline outcome values and other demographic characteristics. Participant measures of perceived change will be compared between groups by calculating the relative risks and their 95% confidence intervals at each time point using log binomial regression.

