### Randomisation and allocation

Following a physical screening examination, volunteers who meet the inclusion criteria will be accepted as participants and undergo baseline assessment at the University of Melbourne. Following baseline assessment, participants will be stratified by treatment site and randomly assigned in permuted block of six and eight to either physiotherapy or placebo treatment groups. The randomisation sequence will be generated using a computer-generated table of random numbers by the study biostatistician (AF). Allocations will be sealed in opaque and consecutively numbered envelopes kept in a locked location. These will be opened in sequence by an independent administrator not involved in eligibility assessment, outcome assessment or treatment. Allocation will be revealed to the treating physiotherapist by fax before the participant presents for treatment.

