### Interventions

Ten musculoskeletal physiotherapists located around metropolitan Melbourne will implement both interventions. All treatments will be individual sessions lasting 30–45 minutes, twice weekly for the first 2 weeks, once a week for the next 4 weeks, then once a fortnight in the last 4 weeks (a total of 10 treatments). Participants will be requested to refrain from seeking other forms of treatment during the trial. However, due to ethical considerations, analgesia will be permitted. Use of medications and other therapies will be recorded in a logbook.

The treatments will be standardized and the therapists will be trained to deliver both treatments prior to the study. A comprehensive treatment manual will be produced and the importance of following the protocol emphasised. For the physiotherapy treatment, it is considered important to allow the therapists to adjust the intensity of the standardised treatment techniques to match the participants' capabilities. Thus the number of repetitions of the exercises can be reduced. Deletion of techniques will be permitted if participants find them too painful. At the end of each treatment session for each participant, the physiotherapist will complete a checklist to ensure compliance with the standard approach.

All participants will be requested not to seek other forms of treatment during the study but use of analgesia will be permitted and recorded in a log-book.

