### Data analysis

All analyses will be conducted on an intention-to-treat principle using all randomized participants. Missing data will be replaced by the last score carried forward. Demographic characteristics and baseline data will be summarised by descriptive statistics. An index will be computed to assess the success of blinding [47]. This index takes the value one for complete blinding and zero for complete lack of blinding.

For outcomes measured using an essentially continuous scale, differences in mean change from baseline to each time point will be compared between groups using linear regression modelling adjusting for baseline levels of the outcome measure. Model assumptions will be checked by standard diagnostic plots [48]. For analysis across all time points simultaneously, accounting for repeated measurements, we will estimate the differences between groups using generalised estimating equation models for the post-baseline measurements with adjustment for baseline measurements, a robust variance and unstructured working correlation [49]. Constancy of the difference between groups over time will be assessed by fitting models which include a term for the interaction between treatment and time. Sensitivity analyses include repetition of analyses with calculation of bootstrap standard errors, and identification of influential individuals by sequentially omitting each participant and refitting the model.

Participant measures of perceived improvement following physiotherapy or placebo treatments will be compared by calculating the relative risks and their 95% confidence intervals at each time point using log binomial regression [50]. Repeated measures relative risk calculations will be performed using generalised estimating equations with a logarithmic link function, robust variance and unstructured correlation [49]. As above, models including a term for the interaction between treatment and time will be fit to assess the constancy of the difference between groups over time.

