We chose a placebo treatment as the comparator rather than no treatment as we wished to evaluate the specific effects of physiotherapy over and above those gained from regular contact with a caring therapist. There is some debate in the literature about whether it is appropriate to use a placebo treatment for interventions such as physiotherapy or acupuncture where it is difficult to isolate the direct and indirect effects of the therapy [58]. It has been argued that these effects are unlikely to be distinct, divisible and additive and that using a placebo controlled trial design will not detect the whole treatment effect and may generate false negative results. However, we believe that the primary goal of physiotherapy is to improve the modifiable impairments associated with CRCP using various techniques and as such it should provide greater benefits than those simply due to the therapeutic environment. The project physiotherapists will treat an equal proportion of experimental and placebo group participants to ensure that any effects of the personality of each therapist and the treatment environment are equally distributed.

It is anticipated that all participants will be recruited by the middle of 2007 with data acquisition completed six months later. The results from this trial will contribute to evidence based recommendations for the effectiveness of a physiotherapy program in the management of CRCP.

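### Allocation is stratified by physiotherapist or site, but no stated model includes that factor, and the abstract and methods give different covariate lists; the result is mildly conservative inference

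*Protocol article*

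**What the plan says.** The stratum has two names. The abstract describes allocation "using concealed allocation stratified by treating physiotherapist". The Randomisation and allocation section says "participants will be stratified by treatment site and randomly assigned in permuted block of six and eight". Under Interventions, "Ten musculoskeletal physiotherapists located around metropolitan Melbourne will implement both interventions", so treatment is crossed with therapist. The Discussion explains that each therapist will treat equal proportions of both groups "to ensure that any effects of the personality of each therapist and the treatment environment are equally distributed".

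The Data analysis section sets out three models:

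- Continuous outcomes at each time point are compared "using linear regression modelling adjusting for baseline levels of the outcome measure".
- Continuous outcomes across time points use "generalised estimating equation models for the post-baseline measurements with adjustment for baseline measurements, a robust variance and unstructured working correlation".
- Perceived change uses log binomial regression at each time point and a log-link GEE across time points, with no covariate named.

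None of these has a physiotherapist or site term. The abstract gives a different covariate set: "linear regression modelling will be applied adjusting for baseline outcome values and other demographic characteristics". In Data analysis, demographic characteristics appear only as something to be summarised descriptively.

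**The concern.** Stratified blocks hold the arms close to balance within each therapist or site, so differences between strata largely cancel out of the treatment contrast. A model without the stratum leaves those differences in its residual variance. Its standard error then exceeds the true sampling variability of the estimate, the interval is wider than the design warrants, and the test runs below its nominal level. The Discussion itself treats therapist and environment effects as plausible, so the factor is a natural covariate.

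The second issue is a plain inconsistency. The same regression has two covariate lists, and the longer one does not name its members. The Outcome assessment section collects several candidates, such as age, sex, symptom duration, medical history and medication use, so a reader cannot tell which model gives the primary estimate.

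**Working it through.** **Inputs from the Sample size section:** difference 10 SPADI units, SD 27, baseline to 10-week correlation 0.45, 91 per group, two-sided 5%, 80% power; repeated-measures power 85% with post-baseline correlation 0.8. **Assumed:** the share of residual SPADI variance lying between strata, written ICC. The documents give no value, so 0, 0.05, 0.10 and 0.20 are used.

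**Step 1: reproduce the plan's figures.**

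- Residual SD = 27 × √(1 − 0.45²) = 24.11.
- n per group = 2 × [24.11 × (1.960 + 0.842)/10]² = 91.3, against 91 stated.
- SE at 91 per group = 24.11 × √(2/91) = 3.575. The noncentrality is 10/3.575 = 2.7975, and power = Φ(2.7975 − 1.960) = 79.9%.
- Repeated measures: variance = 27² × [(1 + 0.8)/2 − 0.45²] = 508.5, which gives 84.9% power against 85% stated.

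The plan's figures stand. Neither calculation has a stratum term.

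**Step 2: closed form, assuming exact balance within every stratum.** Let f = 1/√(1 − ICC) be the ratio of model SE to true SE when the stratum is omitted.

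- Type I error, omitted = 2 × [1 − Φ(1.960 f)]
- Power, omitted = Φ(2.7975 f − 1.960 f)
- Power, included = Φ(2.7975 f − 1.960)

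| ICC | f | Type I, omitted | Power, omitted | Power, included |
|---|---|---|---|---|
| 0 | 1.000 | 5.0% | 79.9% | 79.9% |
| 0.05 | 1.026 | 4.4% | 80.5% | 81.9% |
| 0.10 | 1.054 | 3.9% | 81.1% | 83.9% |
| 0.20 | 1.118 | 2.8% | 82.6% | 87.9% |

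The gain must be read along a row: 1.4 points at ICC 0.05 and 2.8 at 0.10. Setting the right-hand column against 79.9% would overstate it, because 79.9% is the power at ICC 0.

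**Step 3: simulation with real blocks.** Ten strata, blocks of six and eight, 182 participants and 4,000 runs per setting. About 18 participants per stratum often leave a block incomplete, so balance is not exact.

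| ICC | Mean model SE, omitted / included | Type I, omitted / included | Power, omitted / included |
|---|---|---|---|
| 0 | 3.58 / 3.58 | 4.9% / 5.0% | 79.5% / 78.8% |
| 0.05 | 3.57 / 3.49 | 4.4% / 4.8% | 78.9% / 79.9% |
| 0.10 | 3.56 / 3.40 | 4.1% / 5.0% | 79.9% / 82.4% |
| 0.20 | 3.54 / 3.21 | 3.8% / 5.6% | 81.8% / 86.6% |

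The simulation standard error is √(0.05 × 0.95/4000) = 0.3 points for a 5% rate and √(0.8 × 0.2/4000) = 0.6 points for 80% power. From the unrounded SEs, the model without the stratum gives intervals wider by 3.568/3.494 = 1.021 at ICC 0.05 and 3.562/3.403 = 1.047 at ICC 0.10. Further runs with the same block sizes gave type I errors of about 4.5% and 4.2% and power gains of about 1 and 2.6 points. The closed form is therefore an upper limit on the SE error. At ICC 0 the small power difference is within simulation error and reflects at most the cost of nine degrees of freedom.

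**The case against.** **This is a condensed article, and the role of stratification factors is often left to a fuller plan.** That would hold if the article were silent on the models. It specifies them down to working correlation, robust variance and bootstrap sensitivity analyses, and it states two covariate lists and two stratum names. The inconsistencies are on the page, and naming the recorded stratum in models already written out costs nothing.

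**The error is small, safe in direction and rests on an assumed ICC.** This stands. The Interventions section describes standardised treatments, therapist training, a manual and session checklists, all of which make a large therapist share less likely. A reader might infer inflated false positives or a power shortfall. The calculations support neither: type I error is at or below 5%, and closed-form power without the term stays at about the planned 80%. What is forgone is a modest extra gain.

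**The robust variance or the bootstrap already deals with it.** It does not. The robust variance handles repeated measurements within a participant, and a bootstrap that resamples participants without regard to stratum keeps the between-stratum variation.

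**Covariates cannot be picked to suit the result.** A reader might infer from the open list that the primary model could be chosen after seeing which one favours physiotherapy. The Blinding section keeps the data manager and statistician unaware of allocation until analyses are complete, which limits that risk considerably. It does not say which covariates are in the model.

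**Physiotherapist and site may be the same thing.** A reader might infer that the Discussion's claim of equal proportions per therapist fails if the stratum is the site. If each physiotherapist works alone at one site, the two labels describe one stratum and the claim holds. The documents do not settle this, so only an inconsistency of terms is shown.

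**Conclusion.** The point holds as a mild mismatch between design and analysis, together with two inconsistencies of wording. The stated models omit the stratification factor, the factor has two names, and the abstract's covariate list does not agree with Data analysis.

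The consequence is slightly conservative inference without bias. If strata explain 5% or 10% of residual SPADI variance, the SE is up to 2.6% or 5.4% too large, type I error is about 4.4–4.5% or 3.9–4.2%, and including the stratum adds roughly 1 to 3 points of power at 91 per group. These figures rest on the assumed ICC and, for the upper limits, on exact balance within strata. The effect is zero if strata do not differ. No size was computed for the relative risk. The trial's validity is not in question; the change is worth making because it is nearly free and leaves a single primary model.

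**What to change.** 1. Name the stratum once, using the factor actually used for allocation, in both the abstract and the Randomisation and allocation section. If each physiotherapist works at a separate site, say so.
2. Add that factor as a fixed effect, alongside treatment and baseline outcome, in the linear regression and the GEE for continuous outcomes.
3. For the relative risk, include it in the log-link GEE with robust variance, and state that this model also serves when log binomial regression does not converge.
4. Delete the demographic covariates from the abstract's description of the primary model, so that it agrees with Data analysis.

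The cost is wording plus nine degrees of freedom. With 182 participants, the residual degrees of freedom fall from 182 − 3 = 179 to 170. The variable is already recorded at randomisation, so no new data are needed.

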**Other measures**	

Compliance	• Number of therapy visits • Physiotherapy group: Completion of home exercises via log-book
Adverse effects	Log-book and open probe questionning

Average pain, worst pain and pain on three self-selected activities (over the past week) will be measured by separate 11-point numeric rating scales [12] numbered in 1 cm intervals. The amount of weakness, stiffness and interference with activities of daily living (over the past week) will be measured similarly.

Participant perceived global rating of change overall and in pain, strength, and stiffness (since commencement) will be recorded on separate 5 point Likert scales (1-much worse, 2-slightly worse, 3-no change, 4-slightly better, 5-much better). Measuring participant perceived improvement using a rating of change scale has been shown to be a clinically relevant and stable concept for interpreting truly meaningful improvements from the individual perspective [42]. A successful outcome will be defined a priori as 'much better' on the rating scale.

Health-related quality of life will be measured using the Medical Outcomes Study 36-item short form (SF-36) (8 subscales scaled from 0–100 where a higher score represents better health) [43]. This the most widely used generic measure of health related quality of life and permits comparison of the impact of disease and treatment across studies and populations. The clinimetric properties of the SF-36 have been well established on samples from diverse populations [43,44]. We will also use the Assessment of Quality of Life (AQoL) instrument. The AQoL comprises 15 items on ordinal scales with four levels per item covering five dimensions (illness, independent living, social relationships, physical senses and psychological wellbeing). It produces a single utility index that ranges from -0.04 (worst possible health-related quality of life) to 1.00 (full health-related quality of life). The AQoL has strong psychometric properties [45,46]. The AQoL can also be converted into a utility index to calculate quality adjusted life years (QALY).

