### Sample size

Sample size was calculated based upon the ability to detect a 10-point difference in improvement in SPADI score, previously reported to indicate a clinically important improvement (or worsening) of shoulder function [41]. Applying power calculations appropriate for analysis of covariance (adjusting for baseline SPADI score), to detect a difference in 10 week SPADI of 10 units assuming a common between-participant standard deviation of 27 and a baseline to 10 week correlation in SPADI scores of 0.45 (from our pilot study), 91 participants per group will be required to achieve 80% power at a two-sided 5% significance level. Including the 10 week and further 22 week follow-ups in a repeated measures analysis increases the power to 85% assuming a conservative correlation of 0.8 between all post-baseline measurements and a uniform physiotherapy effect. We will allow for a 10% loss to follow-up and aim to recruit 100 participants per group.

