The primary economic evaluation will take the form of a cost effectiveness study with a range of outcome measures including the incremental cost per extra person with a clinically significant improvement in pain, per extra person perceived to be recovered, and per extra quality adjusted life years (using the AQoL over 22 weeks). A social perspective on costs will be taken that includes resource use incurred both by health services and by the participant irrespective of the source of payment. The inclusion of time/productivity gains is controversial and the cost effectiveness ratios will be calculated with and without these indirect costs. All health care costs will be included, however to reduce the impact of extreme values, if inpatient hospital costs are unrelated to CRCP they will be excluded. Standard methods of economic evaluation alongside a clinical trial [51] will be used to evaluate the differences in resource use and health outcomes over 12 months between groups. The statistical analysis of costs data will be similar to outcome data although adjustments for overdispersion may be necessary. Confidence intervals for incremental cost effectiveness will be calculated directly using non-parametric bootstrapping [52]. In addition we will calculate a cost effectiveness acceptability curve based for a range of hypothetical money values of outcomes [53]. This will be done using individual cost and outcome data over the 22 weeks or, if adjustments for imbalance at baseline are necessary, using regression analysis [54]. Hypothetical money values will be taken from the decision making literature but the trial will also ask patients in each arm of the trial their willingness to pay for the treatment prior to and after treatment. This will not only provide money values for the calculation of net benefits but also provide evidence on the influence of health experience on the value of health outcome to patients.

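### The acceptability curve adjusts for baseline only if imbalance is judged to require it; QALYs should always be adjusted for baseline AQoL

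*Protocol article*

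**What the plan says.** All of this is in the protocol article; section names are given.

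- **Economic analysis (Data analysis, last paragraph).** One of the cost-effectiveness measures is incremental cost "per extra quality adjusted life years (using the AQoL over 22 weeks"). Intervals for incremental cost-effectiveness come from a non-parametric bootstrap, and that sentence mentions no adjustment. The acceptability curve comes next, with unadjusted data as the default: "This will be done using individual cost and outcome data over the 22 weeks or". The alternative that the sentence then offers applies only on a condition: "if adjustments for imbalance at baseline are necessary, using regression analysis". The text does not say what makes adjustment necessary or which covariate would be used.
- **Clinical outcomes (Data analysis, second paragraph).** Continuous outcomes are compared by "linear regression modelling adjusting for baseline levels of the outcome measure". No condition is attached.
- **Sample size.** The calculation relies on baseline adjustment, using a SPADI correlation of 0.45 between baseline and week 10, and 0.8 between post-baseline measurements.
- **Visits (Abstract, Methods/Design).** "Blinded assessment will be conducted at baseline and at 10 weeks and 22 weeks after randomisation".

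**The concern.** Baseline AQoL is collected in everyone and is likely to be the strongest single predictor of a participant's QALY. It predicts the later scores and, under the usual calculation, is itself part of the QALY. Adjusting for such a covariate gains precision whatever imbalance happens to be seen, so observed imbalance is a poor trigger. A conditional rule with no criterion also leaves a choice of method open until the baseline data have been examined.

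At stake are the precision of incremental QALYs and the way an ordinary chance imbalance carries into the acceptability curve. The incremental ratio is affected too if its bootstrap is left unadjusted. If the curve were adjusted and the ratio were not, the two would rest on different estimates of the same quantity. Cost-effectiveness is part of the trial's stated aim.

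**Working it through.** **1. The plan's own figure.** With SD 27, difference 10, r = 0.45, two-sided 5% and 80% power:

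n = 2 × 27² × (1 − 0.45²) × (1.960 + 0.842)² / 10² = 91.3 per group.

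This agrees with the stated 91 (power at 91 is 79.9%). The repeated-measures power at 91 per group is 84.9%, against a stated 85%. Without baseline adjustment the requirement would be 115 per group, so the protocol already counts on this gain for SPADI. It gives no precision figure for QALYs.

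**2. Inputs for QALYs.**
- Visit times of 0, 10 and 22 weeks: from the protocol.
- Trapezium rule: assumed, because the protocol says only that the AQoL over 22 weeks is used.
- Equal SD *s* at each visit: assumed.
- Correlation of 0.8 between follow-ups and *r* = 0.45 with baseline: the protocol's SPADI values, borrowed for AQoL. *r* is varied from 0.3 to 0.7.
- AQoL SD of 0.2: assumed, with 0.15 to 0.25 as a range.
- 100 per arm: from the protocol.

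**3. Weights.** The trapezium rule gives 10/2 = 5 weeks to baseline, (10 + 12)/2 = 11 to week 10, and 12/2 = 6 to week 22. Baseline therefore carries 5/22 = 22.7%.

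**4. Variance removed by adjustment.** In weeks:

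- Var(QALY)/s² = 25 + 121 + 36 + 2(55r + 30r + 66 × 0.8) = 287.6 + 170r
- Cov(QALY, baseline)/s² = 5 + 17r
- R² = (5 + 17r)² / (287.6 + 170r)

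| r with baseline | R² | SE ratio, adjusted/unadjusted |
|---|---|---|
| 0.30 | 10.1²/338.6 = 0.30 | 0.84 |
| 0.45 | 12.65²/364.1 = 0.44 | 0.75 |
| 0.50 | 13.5²/372.6 = 0.49 | 0.71 |
| 0.70 | 16.9²/406.6 = 0.70 | 0.55 |

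At r = 0.45, 100 per arm with adjustment is worth about 100/0.56 = 178 per arm without it.

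**5. Shift from a chance imbalance.** The SE of the baseline difference is 0.2 × √(2/100) = 0.0283. The slope of QALY on baseline is 12.65/52 = 0.2433 QALY per unit of utility. A one-SE imbalance moves the unadjusted difference by 0.0283 × 0.2433 = 0.0069 QALY. Of this, 0.0283 × 5/52 = 0.0027 comes directly through the baseline weight; the rest comes through correlation. For SDs of 0.15 to 0.25 the shift is 0.0052 to 0.0086. For comparison, the SE of the QALY difference at SD 0.2 is 0.0104 unadjusted and 0.0078 adjusted. A shift of 0.0069 equals a utility gain of 0.0069/(22/52) = 0.016 held for all 22 weeks.

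**6. The conditional rule.** The protocol gives no trigger, so adjustment was assumed to occur when the baseline test has |t| > 1.96 (40,000 simulated trials, no treatment effect, 100 per arm, r = 0.45).
- Over all trials the rule shows no bias. Its type I error is 3.8% and its variance is 1.56 times that of always adjusting (1.31 at r = 0.3, 2.66 at r = 0.7).
- About 27% of trials have |t| between 1 and 1.96 and stay unadjusted. In these the QALY difference is off by 0.91 of its SE on average, in the direction of the imbalance. Type I error is 8.8%, against 5.1% with adjustment.

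**The case against.** Several points on the other side are sound and limit the claim.

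- **Scope.** The conditional clause follows the acceptability-curve sentence and formally governs that curve. A reader might infer that the protocol forbids or conditions adjustment of every QALY analysis. It does not say so: for the bootstrapped intervals it is silent, and silence in a condensed article is not an error. What stands is that the only adjustment rule written specifically for the economic evaluation is conditional.
- **Already covered.** AQoL is a secondary outcome, so AQoL scores fall under the unconditional clinical rule, and regression is named as an option for the curve. Baseline AQoL is therefore not simply ignored. But the clinical rule concerns change from baseline to each time point, and a QALY accumulated over 22 weeks is not of that form.
- **Bias.** A reader might infer that the planned estimate is biased or inflates false positives. Randomisation prevents that: over all randomisations the rule is unbiased and, under the assumed trigger, conservative. The error is conditional on the imbalance seen. The trigger also uses baseline data, and the statistician stays blinded until analyses are complete, so outcome-driven choice is limited.
- **Reach.** A reader might carry the 44% over to net benefit or the cost-effectiveness ratio. The documents do not support this. For money value λ, Var(net benefit) = λ²Var(QALY) + Var(cost) − 2λCov(QALY, cost), and no cost variance or covariance is given. Nor do the figures apply to the pain-improvement and perceived-recovery measures.
- **Assumptions.** The trapezium rule, the AQoL correlations and the AQoL SD are not in the protocol. A generic utility may track its baseline less or more closely than SPADI does.

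**Conclusion.** The point holds for QALYs and for net benefit based on them. The protocol fixes a conditional rule with no criterion where unconditional adjustment would be better and uses a variable already collected. The loss is one of efficiency, together with an error that follows the observed imbalance.

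Under the trapezium rule, with 0.8 between follow-ups, adjustment removes about 44% of QALY variance at a baseline correlation of 0.45, with a range of 30% to 70%. A typical chance imbalance shifts unadjusted incremental QALYs by about 0.007 at an assumed SD of 0.2, roughly two thirds of their unadjusted SE. The size rests on borrowed correlations. The direction needs only that baseline AQoL predicts later AQoL, and would hold without the direct baseline term. The primary clinical outcomes and the sample size are not affected.

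**What to change.** Replace the conditional clause in Data analysis with a fixed rule: incremental QALYs, and net benefit based on QALYs, are always estimated by regression on treatment and baseline AQoL utility, whatever imbalance is observed. The site stratum used in randomisation may be added. Use the same model inside the bootstrap and for the acceptability curve, so that ratio and curve rest on one estimate. Report the unadjusted result as a sensitivity analysis. State how QALYs are calculated from the three visits.

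The rule need not extend to the pain-improvement and perceived-recovery ratios, for which baseline AQoL is not the obvious covariate. The cost is a change of wording and minor programming, with no new data.
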